Adverse events (e.g., falls, pain, or dizziness) that occur during the study period, whether related to the study intervention or not, will be recorded. In case the training intervention is discontinued for any reason (e.g., hospital discharge, medical complications, or serious adverse event), a participant will not be required to participate in the follow-up assessments. Patients who suffer from a recurrent stroke during the study will be excluded, as will those with any medical condition or disease that occurs during the study and may affect limb movement or mobility. All enrolled patients may undergo outpatient rehabilitation after discharge from the Department of Rehabilitation. The types of rehabilitation treatment during follow-up will be recorded.

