### 2.8. Randomization

The randomization of the enrolled participants for robot-assisted treadmill gait training (RTGT) or therapist-assisted treadmill gait training (TTGT) will be performed as a block randomization with a 1:1 allocation to either RRGT or TTGT. As mentioned above, in randomly selected IS patients with a 1:2 allocation, a repeated multimodal magnetic resonance imaging (MRI) examination, including functional MRI (fMRI), will be performed during the study follow-up.

Participants will be randomized after the screening of eligible participants by the certificated neurologist at the Comprehensive Stroke Centre and before the first clinical visit (visit 1).

Participants will be randomized in a 1:1 ratio and in a 1:2 ratio to multimodal magnetic resonance imaging (MRI) using the web randomization module. A randomized web number generator will be implemented for group allocation. Neurologists will generate the allocation sequences, enroll the participants, and assign the participants to interventions.

The allocation might be adaptively modified in cases when patients randomized for RTGT, after enrolment and during the course of rehabilitation, will be identified as independent walkers (FAC > 3). This change will be reported. It has previously been identified that stroke survivors with gait deficits (FAC ≤ 3) with higher motor impairment are those who benefit the most from robot-assisted therapy in combination with conventional therapy [15,23,47,48].

All participating patients will obtain a card before discharge (visit 2) with the dates of all scheduled outpatient events (visit 3 and visit 4), including the dates of the fMRI examinations and even the telephone contacts with the study investigators (neurologist and principal physiotherapist). All enrolled patients will be promoted and motivated to remain in the study and complete follow-ups during each scheduled visit. In participants who discontinue or deviate from the intervention protocols, the acquired outcome data will be collected for a further subanalysis.

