### 2.10. Statistical Analysis

For the statistical analysis of all tested clinical parameters, gait movement pattern parameters, and extracted imaging parameters, the distribution of the data will first be explored. If normally distributed, a two-factor mixed-model ANOVA will explore the differences between the groups and time points. If not normally distributed, Friedman tests will be used to explore the differences between time points (visits 1–4) within each group and Mann–Whitney U tests will be used to explore the differences between both groups (RTGT and TTGT).

The statistical analysis of fMRI data will include standard preprocessing with subsequent general linear model fitting and a group-wise analysis in the Montreal Neurological Institute (MNI) 152 standard space after the nonlinear normalization of the individual structural MRI data [49]. Significant group effects will be evaluated using an analysis of covariance (ANCOVA) with group, visit, and age as covariates. An atlas-based region of interest (ROI) analysis will be used to evaluate the amplitude and volume of the primary sensorimotor and premotor activations and the laterality index (ipsilesional − contralesional/ipsilesional + contralesional), which are the main secondary outcome measures of the fMRI analysis. Since the functional study design and paradigm partly follow the study of Boyne et al. [32], the choice of regressors and contrasts for the statistical analysis of the corresponding data will likewise follow that study. Structural data (DWI and T1-weighted) will be evaluated in separate pipelines to extract the following parameters from anatomically defined ROIs: regional cortical thickness; fractional anisotropy (FA); and axial, radial, and mean diffusivity (AD, RD, and MD), respectively. Alternative DWI analysis models may include, e.g., FD/FDC or NODDI. The quantitative parameters derived from functional and structural imaging will be included in an extended factor analysis of the global predictors of gait recovery.

With respect to the type of missing variable, the appropriate imputation (e.g., single imputation, multiple imputation, etc.) might be performed if needed [50].

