As data accumulate, the validity and the integrity of the trial will be subjected to an interim analysis after the first 30 participants have been assessed at all four timepoints. The interim analysis, including the first 30 completely measured participants, will guide the final statistical methods. An interim analysis based on 30 participants with complete data will be conducted to perform a power analysis and to compute the final sample size. The principal investigator will have access to the interim results. Additional analyses and further subgroupings are not planned.

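### Randomised patients are excluded for recurrent stroke or a new mobility-related condition, and follow-up is waived once training stops, so the 6-month gait speed comparison may be biased

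*Protocol article*

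**What the plan says.** All references are to the protocol article.

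- **Order of events (2.8).** Patients are randomised after screening and before visit 1, so anything that happens from visit 1 onwards happens to a randomised patient.
- **Exclusion (2.5).** "Patients who suffer from a recurrent stroke during the study will be excluded, as will those with any medical condition or disease". The second group is limited to any such problem "that occurs during the study and may affect limb movement or mobility".
- **Follow-up after stopping training (2.5).** "In case the training intervention is discontinued for any reason (e.g., hospital discharge, medical complications, or serious adverse event"), then "a participant will not be required to participate in the follow-up assessments".
- **Discontinuers and deviators (2.8).** "In participants who discontinue or deviate from the intervention protocols, the acquired outcome data will be collected for a further subanalysis". The sentence before it says that all enrolled patients will be encouraged to stay in the study and complete each scheduled visit.
- **Missing data (2.10).** "the appropriate imputation (e.g., single imputation, multiple imputation, etc.) might be performed if needed".
- **Primary outcome (2.1, 2.6.1).** Gait speed on the 10-meter walking test, up to 6 months. A speed of 0 m/s is recorded when total assistance, or help with limb swing or forward propulsion, is needed.
- **Sample size (2.7).** 60 per group, 85% power, alpha 5%, difference 0.16 m/s, allowing for 15% missing data and a 10% drop in follow-up.

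**The concern.** Randomisation makes the arms comparable only if the patients compared are those who were randomised. Both rules in section 2.5 take patients out because of something that happens afterwards, and the triggers bear directly on walking. The exclusion criterion is itself worded in terms of limb movement and mobility, the domain of the primary outcome. The waiver names medical complications and serious adverse events among its examples. A fall that causes a limb injury could meet the exclusion wording, so harm from either form of training could drop out of the primary result.

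If removal differs between arms in frequency, or in the prognosis of those removed, the 6-month difference mixes a treatment effect with a selection effect. The documents give no removal rates, but the arms do differ in delivery (robotic exoskeleton against manual guidance, section 2.3), and neither participants nor treating physiotherapists are blinded (section 2.4). A later analysis plan could define who is analysed. It could not supply 3- and 6-month gait speeds that were never measured.

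**Working it through.** **1. What happens to each kind of randomised patient**

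| Event after randomisation | Later gait speed | Place in primary comparison |
|---|---|---|
| Recurrent stroke | Not collected once excluded (2.5) | None stated |
| New condition that may affect mobility | Not collected once excluded (2.5) | None stated |
| Training stopped for any reason | Encouraged (2.8) but not required (2.5) | Acquired data go to a subanalysis (2.8); nothing further stated |
| Deviation from the intervention | As scheduled | Acquired data go to a subanalysis (2.8); nothing further stated |

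No section reverses the exclusion.

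**2. The plan's own figure**

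The SD is not given, so the 60 per group can only be solved backwards (two-sided 5%, normal approximation).

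- Evaluable per arm: 60 × 0.85 × 0.90 = 45.9, or 60 × 0.75 = 45 if the losses are added.
- Implied SD = 0.16 × √(n/2) / (1.960 + 1.036). For n = 45.9 this is 0.256 m/s; for n = 45 it is 0.253 m/s.
- Check: an SD of 0.25 needs 44 evaluable per arm, and 44/0.765 = 57.5 (58) or 44/0.75 = 58.7 (59) randomised. So 60 is plausible.

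The plan thus allows for about a quarter of randomised patients to be unevaluable, without attributing that loss to these rules. The allowance protects precision and does nothing about who is lost.

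**3. Bias from removal**

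Let p1 and p2 be the fractions removed in each arm, and D how much slower removed patients walk than retained ones. All three are assumptions. In each arm, the retained mean exceeds the all-randomised mean by p × D. With no true effect, the retained-patient difference is therefore

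bias = (p1 − p2) × D.

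| Removed | D (m/s) | Bias (m/s) | Share of 0.16 | Type I error |
|---|---|---|---|---|
| 5% v 5% | 0.2–0.6 | 0 | 0% | 5.0% |
| 10% v 5% | 0.2–0.6 | 0.01–0.03 | 6–19% | 5.5–9.5% |
| 15% v 5% | 0.2–0.6 | 0.02–0.06 | 12–37% | 6.9–22.9% |
| 25% v 10% | 0.2–0.6 | 0.03–0.09 | 19–56% | 8.9–41.4% |

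The type I error uses SD 0.256 and 60 randomised per arm. For 15% v 5%, 51 and 57 patients remain, and SE = 0.256 × √(1/51 + 1/57) = 0.0493. A bias of 0.04 is then 0.81 SE, and the two-sided rejection rate is 12.8%.

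If D differs between arms, the form is p1 × D1 − p2 × D2. Equal removal is then not enough: 10% in each arm with D of 0.6 and 0.2 gives 0.06 − 0.02 = 0.04 m/s.

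The arm that loses more slow walkers looks better. If the removed patients are faster than the rest, D is negative and the sign reverses.

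**4. Does fuller follow-up add power?**

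At SD 0.2535, 46 per arm gives 85% power and 52 per arm would give 89%. But the six patients added per arm are those assumed to be slower. With D = 0.3 and 6/52 = 0.115 of the arm, the variance is 0.2535² + 0.115 × 0.885 × 0.3² = 0.0643 + 0.0092 = 0.0734, so the SD is 0.271. Power with 52 per arm is then 84.7% (t-test), against 85.0% before. There is no gain.

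**The case against.** The best defence has four parts.

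- **The waiver is a permission, not a bar.** Discontinuers are merely not obliged to return, and section 2.8 encourages every enrolled patient to complete follow-up. This stands in part. It makes the discontinuation half weaker than the exclusion half, but the encouragement does not reach patients whom section 2.5 excludes.
- **Exclusion may mean withdrawal from further participation, not deletion from the analysis, and analysis sets are usually left to an analysis plan that is not shown.** The wording does allow this reading. The later gait speeds are lost on either reading, and that loss is fixed by the protocol.
- **Nothing in the documents shows that removal would differ between arms.** True, and with equal removal and equal prognosis the bias is zero. The concern is a risk that the design accepts without need, not a demonstrated error.
- **Imputation could use the visit 1 and often the visit 2 values.** It could help. But section 2.10 makes it optional, and loss triggered by complications or a new mobility problem is likely to depend on the unseen gait speed even given the earlier values.

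A reader might also infer that sections 2.8 and 2.10 contradict each other, because the latter says "Additional analyses and further subgroupings are not planned". That sentence closes a paragraph about the interim analysis and may be limited to it, and the subanalysis may be additional to the main comparison. The documents do not settle this, and the point does not need it.

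**Conclusion.** The concern holds. Section 2.5 excludes randomised patients for events closely tied to gait speed and waives follow-up after training stops, and no other section keeps the excluded patients in the primary comparison. The 6-month comparison may therefore be biased.

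Confidence is high on what the text says and low on size and direction. The 0.02 to 0.06 m/s for a 10-point imbalance (15% v 5%) rests wholly on assumed removal rates and an assumed gap in gait speed.

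Two stronger readings are tempting and are not supported. A reader might infer that patients are selected on the outcome itself; the rules act on intercurrent events, not on measured gait speed. A reader might also infer that fuller follow-up would raise power; it does not if the recovered patients are slower, as step 4 of the working shows. The reason to change the rules is validity, and the change is needed before follow-up is lost, because it cannot be recovered afterwards.

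**What to change.** - In section 2.5, for outcome purposes, replace the exclusion and the follow-up waiver with a statement that all randomised patients are asked to attend T2 to T4 unless they withdraw consent or die. This includes those who stop training, have a recurrent stroke or develop a new condition.
- State that these patients are analysed in their randomised arm in the primary analysis, and align the section 2.8 sentence on discontinuers and deviators with this.
- Keep the analysis that excludes these events as a sensitivity analysis.
- Add one sentence to section 2.6.1 on how gait speed is scored when a patient cannot attempt the walking test. The existing 0 m/s rule covers only those who need total assistance or help with limb swing or propulsion.

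No treatment rule changes. The cost is protocol wording, some extra follow-up effort and a somewhat larger outcome variance. No power gain should be claimed.

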### 2.6. Study Procedure Outcome Measures

The outcome variables and their study assessments are listed in Table 2.

#### 2.6.1. Primary Outcome

Walking speed is defined as a primary outcome in this study and is the most used outcome measure of walking ability in locomotor rehabilitation. Walking speed has been shown to be a predictor of independence, the functional level at home and within the community, and quality of life [25]. Gait speed will be evaluated before the beginning of inpatient RHB, after two weeks (at the end of inpatient RHB), and during follow-up (three and six months after stroke onset). Gait speed will be measured using the 10-meter walking test. The subject will be asked to walk a distance of 10 m at his/her comfortable speed. The time will be measured for the distance of the middle six meters, which will reflect walking acceleration and deceleration. If the physical assistance of another person (to prevent a fall or collapsing) is needed for a patient to complete the test, the level of assistance will be documented. If total assistance or assistance for limb swing or forward propulsion is required, a walking speed of 0 m/s will be documented [26]. The usage of any assistive device and/or bracing (that patients use for walking and are needed to complete the test) will also be documented. Based on the gait speed, walking may be classified as household (<0.4 m.s^−1^), limited community (0.4 to 0.8 m.s^−1^), or full community ambulation (>0.8 m.s^−1^) [20].

#### 2.6.2. Secondary Outcomes

-Walking dependency

Walking dependency will be evaluated by the functional ambulation categories (FAC) using a 6-point scale ranging from 0 to 5. Scores in the interval <1,3> indicate a dependent ambulator who requires assistance from another person during walking (score 1—continuous manual contact, score 2—intermittent manual contact, and score 3—verbal supervision/guarding). Scores of 4 or 5 indicate an independent ambulator (score 4—independent walking on a level surface and score 5—independent walking on any surface). The FAC has been proven to have excellent reliability, good concurrent and predictive validity, and even good responsiveness in poststroke patients with hemiparesis [27]. The FAC scores have great potential to change significantly after the first 2 weeks of the early inpatient rehabilitation program [27].

-Brain activity related to gait recovery

Specific brain structures with possible impacts on gait recovery in IS patients will be identified using functional magnetic resonance imaging (fMRI) during simple lower limb movements, gait imagery, and gait observation as well as using diffusion-weighted imaging (DWI) and surface-based morphometry. The functional MRI activation magnitude, calculated as the difference in the BOLD signal between task and rest, will be assessed within predefined gait-related brain regions of interest (ROIs), i.e., the sensorimotor cortex, premotor cortex, supplementary motor area, brainstem, and cerebellum. Changes in these ROI parameters over time will be statistically tested within the group, and the regional post-training minus pretraining difference in each group will be submitted to a between-group analysis. Gait recovery after treadmill exercise has been associated with increased task-related activation in the posterior cerebellum and brainstem [28] as well as in the primary sensorimotor cortices and basal ganglia [29]. Moreover, the task-related activation volume in the ipsilesional primary sensorimotor foot representation has been identified as an independent baseline predictor of gait recovery [30]. However, simple leg movements may not be sufficiently representative of a more complex motor behavior such as gait. As it is impossible to directly measure gait-related brain activation in fMRI, gait imagery has been employed as a substitute for real movements in healthy subjects [31] as well as stroke patients with gait impairment [32]. Beyond fMRI, other potential imaging biomarkers include white matter integrity, assessed using diffusion-weighted imaging (DWI), and surface-based morphometry based on structural imaging [33]. So far, according to systematic reviews, evidence for biomarkers based on fMRI, DWI, and structural MRI data remains inconclusive, mostly due to methodological limitations [16].

-Neurological impairment

The National Institute of Health Stroke Scale (NIHSS) represents the most widely used rating scale to evaluate neurological impairment after IS [34]. The NIHSS includes items on consciousness, language, movement, sensation, ataxia, eye movement, the visual field, and others. The scores range from 0 to 42, with higher scores indicating more severe neurological deficits.

-Sensorimotor impairment

The Fugl-Meyer Assessment of Lower Extremity (FMA-LE) is used worldwide and represents the gold standard for the evaluation of poststroke motor impairment [3], both for clinical use and research. The FMA-LE showed excellent intra- and inter-rater reliability in patients early after stroke in an inpatient rehabilitation setting [35]. The FMA-LE consists of five domains (motor function, sensation, balance, joint range of motion, and joint pain) divided into 17 items, with a maximum score of 34 points [36]. Each item is scored on a 3-point scale (0—cannot perform, 1—can partially perform, and 2—can fully perform).

-Biomechanical gait parameters

Biomechanical kinematic and kinetic gait parameters will be evaluated using the instrumented treadmill gait analysis system Zebris FDM-T (Zebris Medical GmbH, Isny, Germany). It has previously been suggested that one of the key questions arising from gait recovery issues is to what extent is the improvement in gait speed the result of behavioral restitution (i.e., motor control improvement in paretic limbs) or the result of more or less fixed compensatory mechanisms (with an asymmetrical gait pattern) [3]. Measuring the biomechanical variables within this study should address this issue. Spatiotemporal gait parameters such as gait speed, cadence, the stance phase duration for the hemiparetic and nonparetic limbs, the step length for hemiparetic and nonparetic limb, and the double stance phase will be expressed as percentages of the gait cycle. Kinetic variables such as the ground reaction force (N) or plantar pressure distribution (N/cm^2^) for both the paretic and nonparetic limbs will also be analyzed. All these parameters will be measured at patients’ preferred speed.

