### 2.7. Sample Size

Based on an analysis of our pilot data concerning the gait velocity (primary outcome), 120 participants (60 in each group) are anticipated to be enrolled in this study. This number of participants would provide 85% power (α level 5%) to detect a difference of 0.16 m/s in the 10 MWT (with respect to a missing data rate of 15% and an expected 10% drop in the follow-ups) between groups after intensive rehabilitation with add-on intervention. The gait speed difference of over 0.16 m/s was previously defined as the minimal clinically important difference in gait speed in subacute stroke patients [46].

For the multimodal magnetic resonance imaging (MRI), including functional MRI (fMRI), we have estimated that a sample size of 50 participants (25 in each group) will suffice to find significant correlations of MRI outcomes with gait recovery. This is based on previous studies of fMRI and gait recovery in similar clinical cohorts [29,32]. We will perform multimodal MRI in half of the randomly selected enrolled IS patients (1:2 randomization), i.e., in 60 participants, to allow for a common drop-out of examined patients with MR images of poor or insufficient quality. As we do not have sufficient information to estimate the variance in the outcomes, we plan to calculate the definitive effect sizes based on the interim analysis of the first 30 subjects measured within all four visits (visit 1–visit 4).

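### The between-arm fMRI comparison uses the post-minus-pre ROI difference without adjusting for the visit 1 value; adjustment costs almost nothing and usually gains precision, by an amount the documents cannot fix

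*Protocol article*

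**What the plan says.** Section 2.6.2 of the protocol article defines activation as the task-versus-rest BOLD difference in predefined gait-related regions of interest (ROIs). Changes over time are tested within each group. For the comparison of the arms, "the regional post-training minus pretraining difference in each group will be submitted to a between-group analysis".

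Section 2.10 describes a further fMRI group analysis: "Significant group effects will be evaluated using an analysis of covariance (ANCOVA) with group, visit, and age as covariates". The pre-training ROI value is not in that list. The same section applies a two-factor mixed ANOVA to extracted imaging parameters, with Mann-Whitney tests between the groups if the data are not normal. Neither uses the pre-training value as a covariate.

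Section 2.5 plans MRI at visits 1 to 4, so the pre-training scan is collected. On the size of the subsample, section 2.7 says "a sample size of 50 participants (25 in each group) will suffice to find significant correlations of MRI outcomes with gait recovery". It plans scanning "in 60 participants, to allow for a common drop-out of examined patients with MR images of poor or insufficient quality". On variability it says "As we do not have sufficient information to estimate the variance in the outcomes".

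**The concern.** When two randomised arms are compared on a change score, the slope of the post-training value on the pre-training value is forced to be 1. Scan measurements in the same person correlate imperfectly, so the best-fitting slope is usually below 1. The forced slope then leaves pre-training noise in the arm contrast. A model with the pre-training value as covariate estimates the slope and removes that noise.

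Precision is at stake in a small comparison. Half the trial is scanned and 25 per arm are expected to be analysable, so a real RTGT-TTGT difference in activation is more likely to be missed than it need be. The information that would help is already in the visit 1 scan.

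**Working it through.** **The plan's own figure.** The 25 per arm in section 2.7 is stated without power, effect size, SD or correlation, and for correlations with gait recovery. There is no power figure for the between-arm fMRI test to reproduce.

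**Inputs.**
- From the article: n = 25 analysable per arm.
- From the article, borrowed: a 5% level. Section 2.7 states it for gait speed only; I take it as two-sided.
- Assumed: correlation rho between the visit 1 and visit 2 ROI values (0.3 to 0.8); ratio k of post-training SD to pre-training SD (0.8 to 1.4); effect size. Age is left out of both models.

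**Formulas.** Set the pre-training SD to 1. The per-participant variance behind the arm contrast is:
- change score: V_c = 1 + k² − 2·rho·k
- adjusted for the pre-training value: V_a = k²(1 − rho²)

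The difference is V_c − V_a = (1 − rho·k)², which is never negative. It is zero only when rho·k = 1, that is, when the true slope is 1. With k = 1 the ratio V_a/V_c is (1 − rho²)/[2(1 − rho)] = (1 + rho)/2, which is 0.75 at rho 0.5.

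Power comes from the noncentral t with noncentrality d/√(2V/n). The change score has 48 df. The adjusted analysis has 47 df, with V_a multiplied by 1 + 1/(2n − 4) = 1 + 1/46 for estimating the slope.

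**Equal SDs (k = 1), effect set so that the change score has 80% power.**

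| rho | V_c | V_a | ratio | adjusted power |
|---|---|---|---|---|
| 0.3 | 1.40 | 0.91 | 0.65 | 93% |
| 0.5 | 1.00 | 0.75 | 0.75 | 89% |
| 0.7 | 0.60 | 0.51 | 0.85 | 85% |
| 0.8 | 0.40 | 0.36 | 0.90 | 83% |

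**Equal SDs, rho 0.5, fixed effects (in cross-sectional SDs).** Change score versus adjusted: 41.0% vs 50.7% at 0.5; 54.7% vs 66.0% at 0.6; 67.9% vs 79.1% at 0.7; 79.1% vs 88.6% at 0.8; 87.7% vs 94.5% at 0.9. The gain is about 7 to 11 points. Simulation at 0.81 SD gave 80.0% vs 89.4%.

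**Unequal SDs, effect again set at 80% change-score power.**

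| k | rho | V_c | V_a | gain (points) |
|---|---|---|---|---|
| 0.8 | 0.5 | 0.84 | 0.48 | +16 |
| 1.2 | 0.5 | 1.24 | 1.08 | +4 |
| 1.4 | 0.5 | 1.56 | 1.47 | +1 |
| 1.2 | 0.7 | 0.76 | 0.734 | about 0 |
| 1.2 | 0.8 | 0.52 | 0.518 | −1 |

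In the last row rho·k = 0.96, so the change score is already almost optimal, and the −1 is the cost of estimating the slope. The direction therefore holds generally, apart from that small cost, while the size depends on rho and k together.

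**The case against.** The best objection is that section 2.6.2 names an outcome variable and not a test. A linear model of the difference on arm with the visit 1 value as covariate gives the same arm estimate, standard error and p-value as a model of the visit 2 value, so the sentence could be read as compatible with adjustment. A condensed article may also leave covariates to a fuller document. This stands in part: the article never says that the comparison is unadjusted. But section 2.10 does list covariates for fMRI group effects and omits this one, and its other imaging analyses do not adjust either. With two visits, the group-by-time test of the mixed ANOVA is itself the change-score test.

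It can also be said that sections 2.6.2 and 2.10 describe different between-group analyses without saying which decides. That is true, and it means that the two-sample change-score test used above may not be the operative one. None of the candidates uses the visit 1 value as a covariate, so the recommendation is the same.

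A reader might infer a fixed loss of about 9 power points. The documents do not support one number: that figure needs rho 0.5, an effect near 0.8 SD and equal SDs at both scans, and none of these is given. A reader might also infer bias from chance baseline imbalance. Under 1:1 randomisation the change-score contrast is unbiased on average. Chance imbalance is already part of its variance, so this is the efficiency loss seen from another side and not a second harm.

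**Conclusion.** The point holds as one of efficiency. The article compares the arms on a post-minus-pre difference, and no stated fMRI analysis adjusts for the visit 1 ROI value. The planned contrast is valid but, apart from one degree of freedom and the small cost of estimating a slope, never more precise than the adjusted one.

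The size rests on assumptions. Under equal SDs the gain is about 13, 9, 5 and 3 points at rho 0.3, 0.5, 0.7 and 0.8, starting from 80% change-score power. If activation is more variable after training, the gain shrinks and can vanish; if it is less variable, the gain grows.

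It might be inferred that 25 per arm is shown to be too few. It is not: section 2.7 justifies that number for correlations with gait recovery and claims no power for a between-arm test. The outcome is secondary, and the gait-speed analysis is not touched.

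**What to change.** In section 2.6.2, specify the between-arm test for each predefined ROI as a linear model of the visit 2 value (or, equivalently, of the change) on arm, with the visit 1 value of the same ROI and age as covariates. Report the adjusted RTGT-minus-TTGT difference with its 95% CI. Keep the post-minus-pre differences as descriptive statistics for each arm. State that this model decides the post-training between-arm comparison, so that it is clear how it relates to the ANCOVA in section 2.10.

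The cost is a sentence or two of wording and one degree of freedom for the visit 1 value. Age is already named as an fMRI covariate in section 2.10. No further scans, patients or data are needed.
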